**8. RANDOMISATION AND BLINDING PROCEDURES**

**Specification on methods and procedures of randomisation**

This is going to be a double blind study. Thus, trial investigators, medical and nursing staff as well as recruited patients will be blinded to allocation.The representative of the sponsor and the principal investigator will get a copy of randomization codes. The information of the randomization codes will then be locked in the database until the time at which an interim analysis or final analysis is performed.

In order to maintain blindness identical packs with identically appearing contents will be used.

When a patient meets ALL inclusion criteria and NONE of the exclusion criteria, he/she can be enrolled in the study. An allocation sequence to one of the above groups will be prepared by the Sponsor of the study. All patients eligible for the study will be randomized to one of the two groups.

A 1:1 treatment allocation will be adopted. Randomization number – and thus the type of formulation – is assigned to each participating patient randomly, depending on the time of arrival to the site and enrollment and ONLY after written informed consent.Randomization data will be kept strictly confidential, only accessible to authorized persons. The blind experiment can cease only due to adverse side events or if essential for the safety of patients. Trial investigators, medical and nursing staff as well as recruited patients will be blinded to allocation.

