**5. Data Collection Procedures**

**5.1 Weaning from cardiorespiratory support**

Weaning from ventilatory support plus extubation (in non-tracheostomised patients) will be attempted, when clinically deemed feasible by the treating intensivist. Level of consciousness, muscle strength, ability to cough and protect airways, renal function and fluid balance will be assessed during an attempt to wean. Successful weaning will be defined as no requirement for ventilatory support for 48 hours after extubation, or (in tracheostomised patients) discontinuation of ventilatory support or no need for ECMO support for 48 hours.

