**Specification on procedures for blindness**

In order to maintain blindness identical packs with identically appearing contents will be used for both placebo and drug administration.

The investigator site personnel involved in the monitoring or conducting of the trial will be blinded to the trial drug codes. Trial drug codes will not be available to the above personnel until after the completion of the trial and final data review, except in the case of an emergency.

Specification on situation, procedures and responsibilities for the unblinding

Randomization data will be kept strictly confidential, only accessible to authorized persons, until the expiry date. Emergency unblinding can occur only due to adverse side events or if essential for the safety of patients. Unblinding is only done when it is deemed essential for the patients by the subject’s physician, by a clinical investigator or by the Data Monitoring Committee.

The investigator should evaluate serious AEs for causality and expectedness as though the patient was on the active drug. Only cases that are considered serious, unexpected and possibly, probably or definitely related (like a SUSAR) would have to be un-blinded for reporting to the competent authorities.

A request for unblinding a subject could be done by:

(a) a physician who is not directly involved in the management of the specific clinical trial

(b) a clinical investigator who is directly involved in the management of the patient in this trial or

(c) the Data Monitoring Committee (DMC). A DMC will have access to unblinded data and can oversee the assessment of emerging risks such as increase in severity or frequency of expected events.

The procedure for unblinding is described below:

- The clinical investigator or treating physician contacts by phone the holder of the code break envelope/list. The on-call 24h authorized representative of the sponsor is designated as the holder of the code break envelope/list responsible for this action.
- The authorized representative of the sponsor provides the CI or treating physician with the information as requested.
- The study code should only be broken when absolutely necessary for valid medical or safety reasons e.g. in the case of a severe adverse event where it is necessary for the CI or treating physician to know which treatment the patient is receiving before the participant can be treated.
- The CI documents the breaking of the codes as per protocol.

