## Interim analysis

Interim analyses will be programmed during the study. Interim analysis of data collected is programmed upon completion of follow-up of the first 15 and 30 patients to eventually discontinue the study in the case of excess adverse events or mortality.

In case of excess serious expected adverse drug reactions, deaths or SUSARs the Data Monitoring Committee will evaluate the results of the analysis in order to decide whether triiodothyronine treatment has provided proof “beyond reasonable doubt” that for all or for some specific type of patients, the trial treatment is clearly contraindicated in term of net difference in mortality and/or adverse drug reactions. Appropriate criteria of “proof beyond responsible doubt” cannot be specified precisely, but in general, a difference of at least 3 standard deviations in *ad interim* analysis of mortality and/or adverse drug reactions would be needed to justify halting or modifying the trial prematurely. In this case, the sponsor will discontinue the study and provide an analytical report to the competent authority within 4 weeks. During interim analysis, the Data Monitoring Committee is obliged to evaluate whether enrolled patients meet the inclusion and exclusion criteria according to the protocol, whether the protocol is being followed, the acceptability of data being accrued, the success of planned accrual targets and the appropriateness of the design assumptions.

Data Monitoring Committee is composed of the representative of the sponsor, Professor of Anaesthesiology [name], Professor of Pharmacology [name], Assistant Professor of Pharmacology [name] and Director and Cardiologist [name].

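### The protocol gives the principal investigator and the sponsor's representative the randomisation codes, contradicting its own blinding statements, and seats the sponsor's representative on the committee that sees unblinded data

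*Protocol*

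**What the plan says.** All references are to the Protocol.

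- **Section 8, methods and procedures of randomisation.** The blind is stated first: "trial investigators, medical and nursing staff as well as recruited patients will be blinded to allocation". The next sentence is "The representative of the sponsor and the principal investigator will get a copy of randomization codes". Then comes the restriction, cut here before its last word: "The information of the randomization codes will then be locked in the database until the time at which an interim analysis or final analysis is". The sponsor prepares the allocation sequence, and numbers are assigned by order of arrival and enrolment.
- **Section 8, procedures for blindness.** "The investigator site personnel involved in the monitoring or conducting of the trial will be blinded to the trial drug codes", and "Trial drug codes will not be available to the above personnel until after the completion of the trial and final data review", except in an emergency. The code-break list is held by an on-call representative of the sponsor. On the monitoring committee: "A DMC will have access to unblinded data".
- **Section 8, breaking the blind at the end of the study.** Unblinding waits for the last patient's last visit and for database lock. The principal investigator of the centre then contacts the committee and is given the allocations on request. The person doing the analysis stays blinded until it is finished.
- **Section 14, interim analysis.** Looks are planned after follow-up of the first 15 and 30 patients. "Data Monitoring Committee is composed of the representative of the sponsor" and four academic or clinical members. Its tasks include judging whether the design assumptions are appropriate.
- **Section 5.1.** Weaning is attempted "when clinically deemed feasible by the treating intensivist". Success requires 48 hours without support.

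**The concern.** A blind holds only if the people who run the trial cannot look up the allocation. Here the document names two holders of the codes whose other duties require them not to have them.

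The principal investigator is, by the end-of-study text, a site-level role. Because numbers follow order of arrival, anyone with the list can foresee the next assignment while the next patient is being considered for consent. That is a loss of allocation concealment, which identical packs do not prevent.

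After randomisation, knowledge of the arm could affect when weaning is attempted, how causality of adverse events is judged, and who is withdrawn. Section 7 lets the investigator end participation when this seems appropriate and replaces withdrawn subjects.

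The sponsor's representative holds the codes and also sits on the committee that sees comparative data and comments on the design. Someone who knows the interim results could then take part in sponsor decisions about design or analysis. A positive result would be harder to defend as double-blind.

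**Working it through.** This is a check of the text, so the statements are set side by side.

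**1. Is the principal investigator blinded?**

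| Place in Section 8 | Does the principal investigator have the codes during the trial? |
| --- | --- |
| Randomisation, blinding sentence (stated twice) | No: trial investigators are blinded |
| Randomisation, code-copy sentence | Yes: receives a copy |
| Procedures for blindness | No, if among the site personnel conducting the trial: codes come after completion and final data review |
| End of study | No: asks for allocations after last visit and lock |

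The last row speaks of the principal investigator of the centre, and the request would be pointless if that person already held the list. One row contradicts the other three.

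**2. Does the database lock resolve it?** Two readings are possible.

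- *The lock covers only the database.* The copies already handed out are unrestricted and the contradiction stands in full.
- *The lock is meant to cover the copies too.* It still opens at an interim analysis. Section 14 plans these after 15 and 30 of 60 patients, that is 15/60 = 25% and 30/60 = 50% of the planned sample. Recruitment and treatment may still be under way. The text does not say for whom the lock opens, and the end-of-study text forbids unblinding before the last visit.

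Neither reading reconciles the passages.

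**3. What does the sponsor's representative see?** This role receives the codes (Section 8) and is a member of the committee (Section 14) that has unblinded data (Section 8). No passage limits the role to blinded material or removes its vote.

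**4. Can the effect be sized?** The protocol's own power figure is not touched by this point. With 30 per arm, 15% against 50%, two-sided alpha 0.05 and pooled variance under the null:

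- mean rate = (0.15 + 0.50)/2 = 0.325
- SE under the null = √(2 × 0.325 × 0.675/30) = 0.1209
- SE under the alternative = √(0.15 × 0.85/30 + 0.50 × 0.50/30) = 0.1122
- z = (0.35 − 1.96 × 0.1209)/0.1122 = 1.007, so power = 84.3%, against the stated 84%.

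The document gives no figure for bias from known allocation. As an **assumption for illustration only**, suppose there is no true effect and knowledge of the arm raises recorded weaning in the T3 group by a fixed number of points. Exact enumeration with 30 per arm and Fisher's test at 0.05 gives these probabilities of a significant result:

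| True rate in both arms | No bias | +5 points | +10 points | +15 points |
| --- | --- | --- | --- | --- |
| 15% | 1.7% | 3.7% | 9.3% | 19.2% |
| 32.5% | 2.6% | 3.8% | 7.7% | 14.8% |

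The table shows that a moderate shift would matter in a trial of this size. It is no evidence that any shift would occur.

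**The case against.** The strongest reply is that much of the blind is intact. Packs and contents are identical for patients and bedside staff. Thyroid hormone samples are assayed only at the end, to protect the blind (Section 5.4). Echocardiograms are read by blinded operators (Section 5.2), and the analyst stays blinded. Randomisation data are said to be accessible only to authorised persons. Serious adverse events are to be judged as if the patient were on active drug. The interim looks are for safety, with no efficacy stopping rule. A sponsor that prepares the sequence, keeps emergency codes and writes the report does not by that fact contradict itself.

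All of this stands, and it rules out some stronger readings that a reader might infer.

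- *That the double blind does not exist.* The document does not support this, because the protections above remain for most people in the trial.
- *That the person deciding on weaning knows the allocation.* No passage says that the principal investigator is the treating intensivist, or that the sponsor or the committee influences weaning. The 48-hour requirement also limits discretion over success, though not over when an attempt is made.
- *That one weaning decision would decide the trial.* A case such as 5/30 against 12/30 (uncorrected chi-square p = 0.045) can be made to lose significance by one extra placebo weaning (6/30 against 12/30, p = 0.091). But it is a boundary case, it is not significant to begin with under Fisher's test, which Section 14 also names (p = 0.084), and the change runs against a bias in favour of T3. It shows that the sample is small and says nothing about access to codes.

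What the reply does not answer is the contradiction over the principal investigator, the unsealed copies, the lock that opens at interim, and the sponsor's seat on the committee.

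**Conclusion.** The point holds as a contradiction that leaves the blind unsecured. The protocol both blinds the principal investigator and hands that person the codes, and its lock sentence does not settle which applies. It also places the sponsor's representative where unblinded comparative data are seen. Allocation concealment and blinding are therefore not guaranteed for a primary endpoint that turns partly on clinical judgement.

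The direction and size of any bias cannot be stated. The rates under step 4 rest on an assumed shift and serve only to show scale. The conclusion about the principal investigator rests on reading that role as the site-level one named in the end-of-study text. If a different person is meant in the code-copy sentence, the general statement that trial investigators are blinded is still contradicted.

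This should be corrected before enrolment, because knowledge of the codes cannot be undone once they have been seen.

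**What to change.** Amend Sections 8 and 14 so that they agree:

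1. Delete the principal investigator from the recipients of the codes.
2. Restrict the codes to the pharmacy study file, or to a sponsor code-break holder with no other role in trial conduct, the monitoring committee or the analysis. State that any copies are sealed.
3. State that the lock opens at an interim analysis for the committee only.
4. Take the sponsor's representative off the committee, or exclude that person from unblinded data and from voting, so that the sponsor receives only the committee's recommendation.
5. Align the randomisation, blindness and end-of-study texts of Section 8 with the interim analysis text of Section 14.

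The cost is amended wording and some reassignment of existing roles. The 24-hour code-break cover needs care. The on-call holder is at present a representative of the sponsor, so that person must be separate from the one on the committee, and the protocol does not say that the pharmacy can provide round-the-clock cover. If the sponsor's representative stays on the committee, a short description of closed sessions must be added, since the protocol has none. Sample size and analysis are unchanged.

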**Specification on procedures for blindness**

In order to maintain blindness identical packs with identically appearing contents will be used for both placebo and drug administration.

The investigator site personnel involved in the monitoring or conducting of the trial will be blinded to the trial drug codes. Trial drug codes will not be available to the above personnel until after the completion of the trial and final data review, except in the case of an emergency.

Specification on situation, procedures and responsibilities for the unblinding

Randomization data will be kept strictly confidential, only accessible to authorized persons, until the expiry date. Emergency unblinding can occur only due to adverse side events or if essential for the safety of patients. Unblinding is only done when it is deemed essential for the patients by the subject’s physician, by a clinical investigator or by the Data Monitoring Committee.

The investigator should evaluate serious AEs for causality and expectedness as though the patient was on the active drug. Only cases that are considered serious, unexpected and possibly, probably or definitely related (like a SUSAR) would have to be un-blinded for reporting to the competent authorities.

A request for unblinding a subject could be done by:

(a) a physician who is not directly involved in the management of the specific clinical trial

(b) a clinical investigator who is directly involved in the management of the patient in this trial or

(c) the Data Monitoring Committee (DMC). A DMC will have access to unblinded data and can oversee the assessment of emerging risks such as increase in severity or frequency of expected events.

The procedure for unblinding is described below:

- The clinical investigator or treating physician contacts by phone the holder of the code break envelope/list. The on-call 24h authorized representative of the sponsor is designated as the holder of the code break envelope/list responsible for this action.
- The authorized representative of the sponsor provides the CI or treating physician with the information as requested.
- The study code should only be broken when absolutely necessary for valid medical or safety reasons e.g. in the case of a severe adverse event where it is necessary for the CI or treating physician to know which treatment the patient is receiving before the participant can be treated.
- The CI documents the breaking of the codes as per protocol.
- On receipt of the treatment allocation details, the CI or treating physician deals with the participant’s medical emergency as appropriate.
- If the treating physician is not the CI, the treating physician must inform the CI of the code break and the reasons for the actions taken as soon as possible.
- The CI documents the breaking of the code and the reasons for doing so on the CRF.
- The authorized representative of the sponsor documents the breaking of the code and the reasons for doing so on the code list within the Pharmacy study file.
- Authorized representative of the sponsor notifies the Research and Development Department in writing as soon as possible following the code break detailing the necessity of the code break and copies to the Coordinator.
- The CI notifies the Research Ethics Committee of the protocol deviation and copies the letter to the Research and Development Department.
- Un-blinded SUSARs will be reported to the appropriate regulatory bodies.

In the event of un-blinding the CI must document the action taken and promptly notify the DMC. Notification must include:

- Name and title of person who requested the code break
- Subject number
- Reason for un-blinding
- Date and time of code break
- Name of person authorizing the procedure
- Signature of person performing the un-blinding.

**Breaking the blind at the end of the study**

The un-blinding of participants cannot occur until all participants have completed the final follow-up (also known as Last Patient Last Visit, LPLV).

Un-blinding should not take place until the database has been locked i.e. all data entered, validated and no further changes are expected. Furthermore, the person performing the statistical analysis will remain blinded until after the analysis has been completed.

Procedure for unblinding at the end of the study is described below:

The principal investigator (PI) of the center contacts the DMC. DMC confirms that the study may be un-blinded by email to authorized representative of the sponsor and provides treatment allocation details to the PI as requested.

If necessary, (e.g. for safety reasons) the PI should make every effort to inform all-participants of their individual treatment assignment.

The PI determines the appropriate method of informing participants of the blinded random assignment.

[figure not shown]

***Figure 7.*** *Schematic plan of serious sdverse drug reactions handling during the trial*

**9. TREATMENT**

### Route of Administration

Intravenous use.

### Maximum duration of treatment of a subject

Each subject will be treated until successful weaning or end of follow up. The maximum treatment duration of a subject may reach 30 days.

### Active comparator products

*Product under investigation:*

T3^®^ Solution for injection 10 μg/ml, each vial contains 150μg of T3 in a total volume of 15ml.

*Placebo:*

Composition identical apart from the active substance.

### Procedures for monitoring subject compliance

Triodothyronine sodium will be administered via intravenous pump and compliance will be monitored continuously during the period of administration from specialized personnel. In addition, measurements of thyroid hormone levels in serum will document both subject compliance and correct practice of the investigators.

##

## Dosage and Safety

## Experimental and clinical data show that maximum efficacy of T3 is achieved when the drug is administered early under hypoxia or hypoxia/reoxygenation conditions where production free oxygen radicals is increased. Thus, the study aims to provide rapid initiation of treatment with T3 within 1 hour of intubation.

## The initial dose for the first 48hours is a high dose of T3 (therapeutic dose) exactly the same with the dose used in ThyRepair trial. Data show that this dose is safe (see below). Administration of T3 beyond 48 hours was not necessary in ThyRepair trial since these patients maintain T3 levels within normal range due to stable hemodynamic status and absence of other stress factors. In ThySupport trial, after the first 48hours, administration of T3 will continue with a maintenance dose which will be reduced by 50%. This is necessary because prolonged mechanical respiratory support and sepsis in these patients inhibit conversion of T4 to T3 and result in sustained reduction in T3 levels.

## Thus, in ThySupport, the dose administered will be 0.8μg/kg i.v. bolus, starting within 60min after respiratory support and will be followed by an infusion of 0.113μg/kg/h i.v. for 48 hours (therapeutic dose). After the first 48h, a maintenance dose will be administered corresponding to 50% of the therapeutic dose (0.057 μg/kg/h i.v.). Drug administration will stop after successful weaning or end of followup (maximum 30 days).

***Figure 8.*** *Schematic of drug administration schedule inThySupport study*

In previous studies in CABG patients it was shown that administration of the dose of T3 proposed here (0.8μg/kg at the end of ischaemia followed by an infusion of 0.113μg/kg/h) resulted in short-term supranormal serum T3 levels without any effects on heart rate or arrhythmias or any other adverse event reported.

[figure not shown]

***Figure 9.*** *Pharmacokinetics of T3 in CABG patients*

More importantly, data from the ThyRepair study (EudraCT: 2016-000631-40) conducted in patients with ST-elevation myocardial infarction showed that administration of the drug under investigation at the proposed doses (0.8μg/kg i.v. bolus followed by an infusion of 0.113μg/kg/h i.v. for 48 hours) resulted in significant increase in the levels of T3 above normal that lasted for 72 hours without any significant adverse event.

[figure not shown]

***Figure 10****: Levels of triiodothyronine in serum during hospitalization in patients after acute myocardial infarction treated with placebo and T3*

Administration of high dose T3 resulted in a non-significant increase in heart rate during the first 3 days (Figure 11).

***Figure 11****: Heart rate assessed during hospitalization in STEMI patients treated with placebo and T3*

***Table.*** *Adverse events during hospitalization in Thy-Repair trial (interim analysis).*

| **Adverse Events** | **placebo Group**  **(n=17)** | **T3 Group**  **(n=16)** |  |
| --- | --- | --- | --- |
| Atrial Fibrillation | 7.7% | 19% | *p=0.25* |
| Thrombus in Left Ventricle | 12% | 12.5% | *p=0.94* |
| Pericardial Effusion | 6% | 6.25% | *p=0.9* |
| Minor Hemorrhages | 12% | 19% | *p=0.57* |
| Diuretics Use during first 24 hours | 40% | 50% | *p=0.7* |
| Need for Sympathomimetics administration after PPCI | 30% | 19% | *p=0.45* |
| Transient Fever wave>37.8 | 0% | 31% | *p=0.01* |

